### Study Design and Population

The study was designed as a randomized controlled trial with 2 arms. In a mid-sized city in the southern part of France, 2 primary schools located in the city’s disadvantaged neighborhood were invited to participate in the study. In France, neighborhoods are classified as disadvantaged on the criterion of income per inhabitant: this income is compared with the average income of the city and that of France. This defines the unfavorable social and economic conditions of the neighborhood and its inhabitants. For example, in the neighborhood considered in this study, the unemployment rate is the highest in the city (26% vs 18%) as well as the prevalence of social housing (49% vs 23%).

Both primary schools agreed to participate in the project. They included children from grade 1 (6 years old) to grade 5 (10 years old) and had never benefited from any intervention in the field of PA. Schools were randomly assigned to either experimental (School A) or control group (School B; see Figure 1). Because the intervention is school based, all the children were included in the study (n=141 for school A and n=148 for school B). Based on studies already published on the same theme, the effects of the intervention are expected to be moderate (standard difference≈0.32, equivalent to an average change in MVPA measurement of 8 minutes per day; SD 18 minutes). In addition, in order to detect a difference of 0.32 with a statistical power of 0.8, a significance level of .05, and a retention rate of approximately 91% with a pre/post comparison, the number of participants should be 70. As a precaution, more children were included. Thus, the number of children enrolled was above the minimum required.

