**Figure 1 figure1:**
[figure not shown]
Flowchart of participants. PA: physical activity; ST: sedentary time.

During the academic year 2016/2017, the following baseline assessments were carried out in these 2 schools: measurements of PA and ST, motors skills, attentional capacities, and academic achievement as well as questionnaires completed by parents. These assessments were carried out in November/December 2016 (T1) and May/June 2017 (T2). Children in both schools had to have parental permission to wear the accelerometer for PA and ST measurement. Motor skills were assessed for all the children at school and their records of academic achievement were collected. The measurements of attentional capacities involved only children in grades 2 and 3.

During the academic school year 2017/2018, the experimental school benefited from a school-based multilevel intervention to increase PA, reduce ST, and make children, parents and teachers aware of the importance of PA for health. This intervention program involved all the children from grade 1 to grade 5. During this interventional year, the same periods of assessment as those carried out at baseline were repeated in November/December 2017 (T3) and May/June 2018 (T4). A final assessment was carried out in June 2019 (T5) after 1 year without any special intervention in the experimental school.

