### Statistical Analysis

STATISTICA version 12.5 (StatSoft/Dell) for Windows and R software will be used. Descriptive statistics of MVPA and ST for the whole day and within the different specific periods of the day will be calculated for both schools at the different assessment times. To examine the effectiveness of the intervention to promote PA and reduce ST, ANOVAs contrasting 2 schools × 5 assessment times with repeated measurement on the last factor will be used on MVPA and ST. Furthermore, chi-square analysis will be carried out to compare the number of children between experimental and control groups who comply with MVPA recommendations for the overall day and during school time.

To explore the longitudinal relationship between PA, motor skills, attention, and academic achievement, multiple regression analyses will be conducted to determine which variables will predict academic achievement scores [47]. We will attempt to examine whether PA or motor variables predict academic achievement through attention. As there are many variables in each category, a principal component analysis will be used to select the variables that are most correlated. Finally, the decision tree process will be used to examine more accurately the longitudinal relationships between the variables selected.

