#### Principal Outcomes From Measurements at Baseline Concerning PA and ST

On average, children aged 8-10 spent 67.20 (SD 17.83) minutes in MVPA and 602.97 (SD 36.32) minutes in ST on weekdays. At different periods of the school day, it appeared that (1) during school time, the international recommendation to spend 30 minutes in MVPA were fulfilled by only 26.92% of the grade 2 children and 5.40% of the grade 5 children. In fact, children spent 22-27 minutes in MVPA during school time while they were sedentary for 260-270 minutes. Thus, it was confirmed that school is a highly sedentary place where PA has to be promoted during recess and also during class time through sedentary breaks and active learning strategies. (2) During lunch time, sedentary activities represented 80% of the period (ie, 88-93 minutes of ST against 10-13 minutes of MVPA), suggesting that this period of the school day could be used for children to be more active and less sedentary through an organizational process. (3) Before school, only 2-3 minutes were spent in MVPA while 22 minutes were ST, suggesting that active transportation to school was scarce or that school is very close to home for some children. Thus, children’s and parents’ sensitization to active transportation should be developed.

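### The chi-square on meeting MVPA recommendations uses no baseline compliance, so with one school per arm a pre-existing school gap could pass for an intervention effect or hide one

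*Protocol article*

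**What the plan says.** The Statistical Analysis section of the protocol article gives two methods for judging effectiveness.

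- For minutes of MVPA and sedentary time: "ANOVAs contrasting 2 schools × 5 assessment times with repeated measurement on the last factor will be used on MVPA and ST".
- For meeting the recommendation: "chi-square analysis will be carried out to compare the number of children between experimental and control groups who comply with MVPA recommendations". This comparison is planned twice, once on the whole day and once on school hours. No time point, baseline term or covariate is named for it.

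Study Design and Population describes two schools, one allocated to each arm, both assessed twice (T1 and T2) before the intervention year. Table 1 gives accelerometry participation for School A and School B: 91 and 121 at T1, 96 and 116 at T2, 45 and 51 at T4, 71 and 86 at T5.

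The section on principal baseline outcomes reports that "children aged 8-10 spent 67.20 (SD 17.83) minutes in MVPA" on weekdays. It also reports that the 30-minute school-time target was "fulfilled by only 26.92% of the grade 2 children and 5.40% of the grade 5 children". Neither figure is split by school.

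**The concern.** A chi-square between two schools at one wave asks whether the proportions differ at that wave. It does not ask whether they changed differently. With many randomised units the two questions give similar answers. With two units, randomisation still balances in expectation, but the single allocation made may leave a sizeable gap, and nothing in this test corrects for it.

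The error can go either way. A school that was already more active can appear to have benefited, and a school that started lower and improved can appear no different from the control. The article collects the two pre-intervention waves that would allow a correction, and its analysis of minutes uses them. The binary endpoint does not, although whether children meet the recommendation is a result that policy readers are likely to pick up.

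**Working it through.** The article gives no operating characteristics for the chi-square, so there is no stated figure to reproduce. The check asks how often the test rejects at a nominal two-sided 5% when the intervention does nothing and the schools simply differ.

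**Inputs from the article.** Weekday MVPA has mean 67.20 and SD 17.83 minutes (ages 8-10, schools combined). The daily recommendation is 60 minutes. Accelerometry counts are 45 and 51 at T4, and 71 and 86 at T5.

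**Assumptions not in the article.** MVPA is normal; the weekday figures for ages 8-10 apply to all wearers; every child counted in Table 1 is analysable; the school gap is constant over time. Gaps of 0, 5 and 8 minutes are chosen for illustration. Eight minutes equals the whole intervention effect the article expects, so it is a large gap.

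**Step 1: compliance.** P(MVPA > 60) = 1 − Φ((60 − mean)/17.83).
- Mean 67.20: 1 − Φ(−0.404) = 0.657
- Mean 62.20 (5 lower): 1 − Φ(−0.123) = 0.549
- Mean 59.20 (8 lower): 1 − Φ(0.045) = 0.482

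**Step 2: rejection probability.** Let d be the difference in proportions, SE0 the pooled standard error and SE1 the unpooled one. Then the probability is about Φ((d − 1.96·SE0)/SE1), plus a negligible opposite tail when d is well above zero.

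Worked case: T4, 5-minute gap, School B lower.
- d = 0.657 − 0.549 = 0.108
- Pooled proportion = (45 × 0.657 + 51 × 0.549)/96 = 0.600
- SE0 = √(0.600 × 0.400 × (1/45 + 1/51)) = 0.100
- SE1 = √(0.657 × 0.343/45 + 0.549 × 0.451/51) = 0.099
- (0.108 − 0.196)/0.099 ≈ −0.89, so the probability is about 0.19

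| Assumed gap | Compliance | T4 (45 vs 51) | T5 (71 vs 86) |
|---|---|---|---|
| 0 min | 66% vs 66% | 5% | 5% |
| 5 min | 66% vs 55% | 19% | 28% |
| 8 min | 66% vs 48% | 41% | 60% |

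Simulation gives the same values. With a continuity correction, the 5-minute row falls to 14% and 22%, and the 8-minute row to 33% and 53%.

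**Step 3: masking.** If School A starts 8 minutes lower and truly gains 8 minutes, both schools end at 66% compliance. The post-intervention chi-square then rejects about 5% of the time, as if nothing had happened.

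**Step 4: does using baseline help?** In a simulation at the T5 counts, with no intervention effect and an assumed latent within-child correlation of 0.5, pre-existing gaps of 10, 15 and 20 percentage points gave chi-square rejection of about 26, 51 and 75%. A between-school comparison of change from baseline rejected in 4.9, 5.1 and 5.0%. This assumes that the same children are measured at both waves.

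**The case against.** The strongest reply is that effectiveness is judged first by the repeated-measures ANOVA, and the chi-square is an added comparison. That stands. In the ANOVA a stable school difference goes into the school main effect and not into the school-by-time interaction, so the concern is confined to the binary endpoint.

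A second reply is that the time point and any adjustment belong in a fuller plan. The time point may. But the article names the method, and a chi-square between groups has no place for baseline or covariates. Running it at T1 and T2 as well would reveal a gap but would still not compare change between schools.

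Third, both schools lie in the same disadvantaged neighbourhood and neither had an earlier physical activity intervention, so a large gap may be unlikely. That is fair; the gaps above are assumptions.

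Three stronger readings are tempting but not supported:

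- **That an existing difference will be reported as an effect.** The article shows no baseline compliance by school and does not say that the chi-square alone will decide effectiveness. It also promises descriptive MVPA and sedentary time for both schools at each assessment, which would show a gap in minutes.
- **That repeated measurement invalidates the test.** At a single wave each child counts once and the standard error is not affected by repetition. It would be wrong only if waves were pooled, which the article does not state. Otherwise the cost is lost information.
- **That grade confounding is shown.** The 26.92% and 5.40% concern the 30-minute school-time target, not the daily 60 minutes. Table 1 does not break wearers down by grade, so neither a grade imbalance between schools nor a shift in grade mix over time is documented. The figures are a reason to include grade in the model and no more.

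**Conclusion.** The point holds for the supplementary compliance endpoint, for the overall day and for school time. The planned chi-square cannot separate a pre-existing school difference from a difference in change, and one school per arm gives no assurance that such a difference is small. The percentages computed here are for the daily target only. They measure a risk under the listed assumptions, mainly the assumed gap, and not a bias known to exist; its direction is also unknown. The analysis of MVPA and sedentary minutes is not affected. The change is worth making because the necessary data were collected and it brings the binary endpoint into line with the analysis of minutes.

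**What to change.** Replace the chi-square with a mixed-effects logistic model or GEE for meeting the recommendation, fitted separately for the overall day and for school time. Include school, time, school-by-time and grade, with clustering by child and all waves used. Report the between-school difference in change from the pre-intervention waves to T4, and to T5, as an odds ratio and a risk difference with confidence intervals. Show raw counts per school and wave, including T1 and T2, as description only.

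State beside the result that the model removes only stable baseline differences. With one school per arm, school-specific time trends stay confounded with the intervention, and no child-level model can separate them.

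The cost is one more model for each of the two endpoints and a less simple test. No new data are needed, and R is already among the listed software. The Results section says that the analyses are close to completion, so the change should be recorded as made at that stage.

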### Intervention Program

Because interventions that are integrated and multileveled seem to be more effective in triggering behavioral changes concerning the levels of PA and ST, this program has been conceived as a school-based approach with interventions at different levels of factors that influence children’s behaviors [3,18,19]. More specifically, it is directed to the children (intrapersonal level), but also to their teachers and parents (interindividual level) and to their environment (physical and organizational levels). Furthermore, to be integrated, it has to be adapted to the real needs of the particular population to which it is dedicated. Thus, PA and ST data from the baseline assessment were analyzed to tune and adapt the intervention program.

#### Principal Outcomes From Measurements at Baseline Concerning PA and ST

On average, children aged 8-10 spent 67.20 (SD 17.83) minutes in MVPA and 602.97 (SD 36.32) minutes in ST on weekdays. At different periods of the school day, it appeared that (1) during school time, the international recommendation to spend 30 minutes in MVPA were fulfilled by only 26.92% of the grade 2 children and 5.40% of the grade 5 children. In fact, children spent 22-27 minutes in MVPA during school time while they were sedentary for 260-270 minutes. Thus, it was confirmed that school is a highly sedentary place where PA has to be promoted during recess and also during class time through sedentary breaks and active learning strategies. (2) During lunch time, sedentary activities represented 80% of the period (ie, 88-93 minutes of ST against 10-13 minutes of MVPA), suggesting that this period of the school day could be used for children to be more active and less sedentary through an organizational process. (3) Before school, only 2-3 minutes were spent in MVPA while 22 minutes were ST, suggesting that active transportation to school was scarce or that school is very close to home for some children. Thus, children’s and parents’ sensitization to active transportation should be developed.

#### PA and ST Intervention Program

According to the socioecological model and to the analyses of PA and ST at baseline, specific intervention actions have been carried out at the different levels of the model. Their content and objectives are detailed in Table 2.

The timings of these actions were coordinated across the different levels of the model. Thus, the contents of the different workshops for the children and the parents were coordinated with the training for the teachers. For example, workshops 1-3 for children took place at the same time of year as sensitization workshops 1 and 2 for parents and training workshop 1 for teachers in order to allow children to discuss and exchange views on these subjects (“what is PA?”, “what is ST?”) with the adults around them and for the teachers to reactivate part of the knowledge when they had the opportunity. Then, feedback from the baseline assessment of PA and ST levels and motor skills was given to the children, parents, and teachers. This was coordinated with workshops 5 and 6 for the children. This led to actions, learning, and discussions with the different actors (ie, children, parents, and teachers) in order to increase PA and decrease ST. Thus, around that time of year, children explored and tested concrete “activities in the schoolyard,” parents came to sensitization workshop 3 (How can I influence my child’s PA?), and teachers were trained in active classroom and sedentary breaks (training workshop 2). This training was followed by a demonstration of these activities in the class (Active classroom and sedentary breaks). Furthermore, during training workshops 3 and 4, teachers discussed strategies to increase children’s PA and the different factors that can influence it. In parallel, some environmental adaptations were carried out. As noted earlier, the baseline assessment led the research team to realize that lunch time was highly sedentary (80% [~95 minutes] of the 120 minutes lunch) when it should be devoted to some active leisure. Therefore, discussions were held with the different staff working in the canteen to reorganize this time so that children spent less time sitting and more time playing and moving (Organizational modification of lunch break). In parallel, a discussion was carried out with the teachers to optimize the organization of the different areas of the schoolyard based on the games to allow children to find their favorite activity and then be more active (Organizational modification of recess games).

Around the middle of the school year, delineations of games in the schoolyard were created by the education department of the town hall (physical and material modifications of the schoolyard), following a participatory bottom-up approach. In fact, the first ideas came from the children (workshop 4: each child drew what he wanted to have in his schoolyard) and then a first selection was done at the class level (design of the schoolyard from the different individual suggestions). Finally, a consultation between the teachers, the research team, and the representatives of the town hall led to the final choices. Furthermore, discussions were carried out on the role of the surrounding environment in facilitating or preventing PA practice at the children’s level with the “photovoice workshop,” as well as at parents’ level (sensitization workshop 4) and at teachers’ level (training workshop 4).

To conclude the intervention, assessments were made with children (workshop 7), parents (sensitization workshop 5), and teachers (training workshop 5) to discuss the behavioral changes that took place and the strategies that were put into place (what worked well or what didn’t?). A drawing contest was organized among children (workshop 8): they were asked to draw themselves in an active situation, and their drawings were presented to the education community and the parents at the end of the school year.

Finally, different political levels were involved during the intervention, such as the different services of the city town hall and the French national education system, which allowed the research team to conduct its actions.

**Table 2 table2:** The different axes of the intervention: content and objectives.

Theme of each action according to the level of the socioecological level				Content	
**Intraindividual (level 1): children**					
		Workshop 1: “What is PA?”		Information about PA was given: the different intensities, the principal differences between PA and sport, and the benefits of PA on health.	
		Workshop 2: “How to practice PA?”		Different activities were presented to the child to be more active at school, in his/her neighborhood, in a sports club, and at different moments of the day.	
		Workshop 3: “What are sedentary habits?”		Information about the different sedentary behaviors that children can have in a day was given, as well as the effect of cumulative ST on health. The possibilities to decrease ST at each time of the day were analyzed.	
		Workshop 4: “What would you like to draw on the schoolyard to play, run, and have fun?”		Children had to draw schoolyard equipment and materials that they would like to have, to allow them to have fun and to move around. These proposals were then studied in each class, classified, and selected to make a proposal per class.	
		Workshop 5: “How does the accelerometer measure PA and ST?”		The mechanical operation of the accelerometer was studied. The data from the accelerometer were analyzed. The children determined their compliance with the WHO guidelines.	
		Workshop 6: “Do I practice enough PA every day to be healthy?”		An analysis of the time devoted to the practice of PA and ST every day was made for each child. Discussions were held with the children about these data and strategies to further increase PA and decrease ST. They identified and worked on barriers to PA practice.	
		Workshop 7: “Have I changed my PA practice? Am I trying to be less sedentary?” and “What did I learn about PA and ST?”		An assessment was made with children on behavioral changes in terms of PA and ST and on the knowledge acquired on PA, ST, and more generally on health.	
		Workshop 8: Drawing contest		A drawing contest on the theme “I’m moving” was done at the end of the intervention period.	
		Activities in the schoolyard: “What games can I play...?”		A session was organized in the schoolyard to identify games that can be played in the schoolyard or in leisure time, alone or with friends. For example: “what games can I play with a cord?” The children imagined and listed games and demonstrated them.	
		Active classroom: “Spelling and mathematics”		Demonstration of active classroom workshops for further use by the teachers: “Spelling activity,” in which children had to touch different parts of the body while spelling out the letters of words. The words were more or less complicated depending on the grade of the children. (2) “Arithmetic exercise,” in which children had to make a jump after having said the result of the addition or multiplication.	
		Sedentary breaks: “Relaxation and breathing”		The activity break included breathing, relaxation, and visualization exercises, or body movements such as motor coordination, balance, and flexibility exercises. These sedentary breaks did not include academic knowledge.	
		Activities outside of school: Photovoice workshop		Excursion to the school neighborhood to observe the areas in which one can practice PA and to identify the areas dangerous for practice. The children took pictures of the different areas with tablets. Back in class, the children showed their photos to their classmates and explained why they took this picture (if it was possible to practice PA in this area, or if it was a dangerous area).	
		Feedback		Individual summary sheets with PA and ST levels and performance at the different motor tests were given to each child in a graphic format after each assessment. Explanations and consideration took place in the classroom.	
